### Stratified Analysis

All objectives will be assessed in the following stratified analyses: (i) by sex; (ii) depending on whether patients have undergone thrombectomy; (iii) depending on whether patients have undergone thrombectomy and treated with rtPA; (iv) whether patients have undergone thrombectomy or treated with rtPA; and (v) number of cycles of inflation and deflation finished to evaluate a possible dose-response effect.

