## Introduction and Rationale

Stroke is one of the leading causes of death worldwide and the main cause of disability (1). Currently, the only therapies for acute ischemic stroke (AIS) patients are the administration of rt-PA (2) and/or endovascular treatment (3). Unfortunately, many patients cannot benefit from these therapies due to their contraindications or evolution time. Neuroprotective therapies could not only increase the benefits of available reperfusion therapies but also provide an option for patients who are not candidates for these treatments (4). However, most neuroprotection trials have so far failed to demonstrate their efficacy in AIS patients, despite promising results in animal studies (4). Remote ischemic perconditioning (RIPerC) represents a new paradigm in neuroprotection (5). It potential upregulates endogenous defense systems to achieve ischemic tolerance in brain ischemia (6). It consists of brief episodes of transient limb ischemia. According to studies in coronary ischemia, RIPerC during the ischemic event is safe, feasible, and related to a decrease in myocardial injury (7). However, there is limited data about the clinical utility of RIPerC in AIS patients. Only four randomized clinical trials (RCTs) have been completed and published (8–11). All of them demonstrated that RIC is safe and feasible in AIS. One has been conducted to test RIPerC in a prehospital setting in AIS patients and as an adjunct treatment with intravenous alteplase (11). Two other small-size studies were only designed to evaluate the safety and feasibility of RIC in AIS patients recruited within 24 h of onset of symptoms (8) and in alteplase treated patients (9). The last and the largest study included 188 patients with confirmed carotid ischemic stroke within 6 h of symptoms onset (10). None of them demonstrated a significant clinical effect or a significant effect on brain infarction volume growth.

We aim to conduct a multicentre study of pre-hospital RIPerC in AIS patients applied within 8 h of stroke onset. Our hypothesis is that RIPerC would be safe and would induce endogenous neuroprotective phenomena associated with good outcomes in AIS patients treated with revascularization therapies or not.

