### Sample Size Estimates

A sample size of 280 subjects in each arm achieves 80% power to detect treatment differences of 14% between the intervention and the control groups, using a two-sided binomial test at significance level of 0.05, assuming that 40% of the control patients will experience good outcome defined by a mRS score of 2 or less at 90 days, and allowing a misdiagnosis rate of 29% (15% of haemorrhagic strokes and 14% of mimic stroke conditions). Two extra interim analyses will be performed at 33 and 67% of recruitment on the primary outcome. Early stopping is planned if large differences between the study groups are observed in order to reduce study participants' exposure to the inferior study arm and saving time and resources. Since repeated significance testing on accumulating data will be performed, adjustment of the usual hypothesis testing procedure to maintain the overall significance level of 0.05 will be done by using the flexible type I error spending function (18, 19). Due to the interim analyses, the sample size must be increased by an inflation factor of 1.02, resulting in 572 patients (286 per group).

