### Statistical Analyses

Included patients will be described with respect to demographic and clinical characteristics, according to the study arm. Continuous variables will be summarized using means and standard deviations for normally distributed data; or median and 25–75% percentiles for non-normally distributed data. Normal distribution will be assessed by means of the Shapiro–Wilks test, rejecting normality when *p* <0.05. Categorical data will be summarized using counts and percentages. Comparisons will be performed by means of the Pearson's chi-squared test for categorical variables; the *t*-test for normally distributed data; and the Mann–Whitney *U*-test for non-normally distributed data.

Primary analysis will be performed by means of the binomial test. If the study groups are unbalanced, the primary outcome will be compared using a logistic regression model that will include the variables exhibiting baseline differences as covariates.

Secondary outcomes will be compared using the most appropriate test according to the distribution of the data. As with the primary analysis, secondary outcomes and safety outcome analyses will be conducted using multivariable generalized linear models with suitable links.

The analysis will be performed on the intention-to-treat set and will be repeated on the per-protocol set as a sensitivity analysis.

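### Separate analyses by sex cannot show whether the effect differs by sex; one treatment-by-sex model for the primary outcome would (minor)

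*Protocol article*

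**What the plan says.** The Stratified Analysis section fixes both a method and a scope: "All objectives will be assessed in the following stratified analyses: (i) by sex". The other four stratifiers are thrombectomy, thrombectomy together with rtPA, thrombectomy or rtPA, and the number of cycles finished, the last described as a look at dose-response. The scope takes in the primary outcome (mRS of 2 or less at 90 days) and the seven numbered secondary outcomes.

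The Statistical Analyses section says how outcomes are compared. The primary outcome uses a binomial test, or logistic regression adjusted for variables that are unbalanced at baseline. For the rest: "Secondary outcomes will be compared using the most appropriate test according to the distribution of the data", with multivariable generalized linear models also mentioned. As described, these all compare the two arms. No term for treatment by sex appears.

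The Sample Size Estimates section describes type I error control for the interim looks at the primary outcome, "to maintain the overall significance level of 0.05". It does not address strata.

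**The concern.** The useful question about sex is whether the treatment effect differs between women and men. Two separate comparisons, one per sex, do not answer it. Each asks whether there is an effect in that sex, with roughly half the patients. When the effect is the same in both, one comparison will often fall below 0.05 and the other above it by chance alone.

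At stake is how a successful trial is reported. The design is powered for the whole sample. If its own assumptions are exactly right and the benefit is uniform, the stratified results can still suggest that it is confined to one sex. Sex is also the only one of the five stratifiers fixed before randomisation, so it is the one where a clean comparison of effects is available and should be used.

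**Working it through.** **Inputs from Sample Size Estimates**
- Test: "using a two-sided binomial test at significance level of 0.05".
- Power and effect: "achieves 80% power to detect treatment differences of 14% between the intervention and the control groups".
- Control rate: "assuming that 40% of the control patients will experience good outcome defined by a mRS score of 2 or less at 90 days", so 40% versus 54%.
- Misdiagnosis: "allowing a misdiagnosis rate of 29% (15% of haemorrhagic strokes and 14% of mimic stroke conditions", so 71% are confirmed ischaemic strokes.
- Final size: 286 per arm (572 in total).

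**Assumption:** the share of each sex is not given. I take 50/50 and show 40/60.

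**1. Reproduce the plan's own figure.** With p1 = 0.40, p2 = 0.54 and mean 0.47:

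n = [1.96·√(2·0.47·0.53) + 0.842·√(0.40·0.60 + 0.54·0.46)]² / 0.14² = [1.96·√0.4982 + 0.842·√0.4884]² / 0.0196 ≈ 198.3, so 199 per arm.

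199/0.71 = 280.3, against 280 stated. 280 × 1.02 = 285.6, rounded to 286. The sample size reproduces.

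**2. Power overall and within one sex.** For m patients per arm:

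power = Φ{[0.14·√m − 1.96·√0.4982] / √0.4884}

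| Patients counted | m per arm | Power |
|---|---|---|
| Whole trial, confirmed strokes (286 × 0.71) | 203 | 81% |
| Whole trial, all randomised | 286 | 92% |
| One sex at 50/50, confirmed strokes | 101.5 | 51.6% |
| One sex at 50/50, all randomised | 143 | 66.1% |
| 40% sex, confirmed strokes | 81.2 | 43.1% |
| 60% sex, confirmed strokes | 121.8 | 59.2% |

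The rows for all randomised patients suppose that the 14-point benefit applies to everyone, including those later found not to have an ischaemic stroke.

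**3. Chance that exactly one sex reaches p<0.05 when both truly gain 14 points.** The sexes are independent samples, so with powers P and Q:

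P(1 − Q) + Q(1 − P)

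- 50/50, confirmed strokes: 2 × 0.516 × 0.484 = 0.50.
- 50/50, all 286 per arm: 2 × 0.661 × 0.339 = 0.45.
- 40/60, confirmed strokes: 0.431 × 0.408 + 0.592 × 0.569 = 0.51.

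If there is no effect at all, exactly one sex is significant with probability 2 × 0.05 × 0.95 = 9.5%.

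**4. What the interaction test offers.** Under a uniform effect it is positive in 5% of trials by construction. Its power at 50/50, with 101.5 confirmed strokes per arm per sex, on the risk-difference scale:

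- 14 points in one sex, 0 in the other: SE = √[(0.40·0.60 + 0.54·0.46)/101.5 + (2·0.40·0.60)/101.5] = √(0.9684/101.5) = 0.0977. Then 0.14/0.0977 = 1.43 and Φ(1.43 − 1.96) = 30%.
- 28 points versus 0: SE = √[(0.40·0.60 + 0.68·0.32 + 0.48)/101.5] = 0.0961. Then 0.28/0.0961 = 2.91 and Φ(2.91 − 1.96) = 83%.

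**The case against.** The strongest reply is that this is one sentence in a condensed article. Interaction terms, multiplicity rules for subgroups and an exploratory label are commonly left to a full protocol or SAP, neither of which is shown. That stands: their absence is not counted here. What remains is what the article does fix, namely separate stratified analyses as the method and all objectives as the scope.

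It can also be said that the section speaks of assessment and does not promise a p-value in each stratum, and that generalized linear models could carry an interaction term. Both are true. The frequencies above therefore apply only if each sex is tested at 0.05, which is the natural result of applying the listed comparisons within strata but is not spelled out.

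Several stronger readings are tempting, and the documents do not support them:
- A reader might infer that chance differences between strata will be reported as effects in some patients only. The article states no such rule of interpretation, so that is a prediction.
- A reader might take the Introduction's phrase "associated with good outcomes in AIS patients treated with revascularization therapies or not" as hypotheses by treatment subgroup. The Discussion and the Summary and Conclusions show that it describes one all-comers population.
- A reader might multiply outcomes by strata and conclude that a false positive is close to certain. Such figures rest on assumed stratum shares, assumed correlations between outcomes and a finer split of the outcome list than the seven numbered secondary outcomes.
- A reader might fault the lack of a testing order for secondary outcomes. The article makes no confirmatory claim for them, and a fixed order would be a design preference.

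Finally, an interaction model is no general remedy. Thrombectomy, rtPA and cycles completed become known only after randomisation, and completed inflation cycles have no evident counterpart in the sham arm, which receives no inflation. This limit stands.

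**Conclusion.** The concern holds in a narrow form and is minor. Separate analyses by sex are the wrong tool for asking whether the effect differs by sex. With a uniform 14-point benefit and a roughly even sex split, exactly one sex would reach p<0.05 in about 45% (all 286 per arm) to 50% (71% confirmed strokes) of trials; at 40/60 with confirmed strokes it is 51%. These figures rest on the plan's 40% versus 54%, the assumed sex split and a two-sided 0.05 test in each sex. Stratifying all objectives five ways is also broader than the data can support. The primary analysis, the alpha spending and the sample size are not affected.

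**What to change.** In Stratified Analysis, for the primary outcome, replace separate testing by sex with one model containing treatment, sex and their interaction. State the scale (odds ratio or risk difference), report the interaction estimate with its 95% CI, and show the effect in women and in men as estimates with CIs, without separate tests.

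Limit the stratified analyses to the primary outcome, or state that those of other outcomes are descriptive.

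Do not present the interaction model as a cure for the thrombectomy, rtPA or cycles-completed strata. Because these form after randomisation, they need separate treatment.

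The cost is a change of wording and one model term, with no new patients or data. The downside is low power, about 30% to detect 14 versus 0 points, so a non-significant interaction must not be read as proof that the effect is the same in both sexes.

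### The reperfusion strata are not limited to confirmed ischaemic stroke, so reperfusion status is confounded with diagnosis and an equal benefit would look smaller in non-reperfused patients

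*Protocol article*

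**What the plan says.** Patients are randomised and treated in the ambulance; the Discussion accepts that the diagnosis is settled only at the hospital. Sample Size Estimates plans for this by "allowing a misdiagnosis rate of 29% (15% of haemorrhagic strokes and 14% of mimic stroke conditions").

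Statistical Analyses states: "The analysis will be performed on the intention-to-treat set", with a per-protocol repeat as a sensitivity analysis. Neither set is defined in the article.

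Stratified Analysis applies five splits to all objectives. Three concern reperfusion: (ii) thrombectomy, (iii) thrombectomy together with rtPA, and (iv) "whether patients have undergone thrombectomy or treated with rtPA". No diagnostic restriction is attached to any of them.

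Table 2 records both AIS confirmation and reperfusion therapies. Its footnote keeps patients with intracranial haemorrhage to 90 days. Patients without evidence of brain ischaemia are followed to discharge and through registries.

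The Introduction places the hypothesis in ischaemic stroke patients with or without revascularisation. Part of the rationale for neuroprotection is that it could "provide an option for patients who are not candidates for these treatments".

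**The concern.** Thrombectomy and rtPA are treatments for ischaemic stroke. Haemorrhages, and most mimics, will therefore be on the 'no' side of each split. The 'yes' side is then almost entirely ischaemic, while the 'no' side mixes ischaemic and non-ischaemic patients. Comparing the two sides compares diagnoses as well as reperfusion status.

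This does not require RIPerC to influence who is reperfused. It is a matter of case mix, separate from the usual caution about splitting on an event after randomisation.

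Splits (ii) to (iv) are the only analyses in the article that address whether RIPerC works with and without revascularisation. The contaminated side is the one that represents non-candidates. If the benefit were the same in all ischaemic patients, the tables could still suggest that it depends on reperfusion.

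**Working it through.** **Inputs from Sample Size Estimates**
- Control rate of good outcome 40%, difference 14 points (so 54% with RIPerC), two-sided 0.05, power 80%.
- Misdiagnosed 29%: 15% haemorrhage and 14% mimic. Ischaemic share 1 − 0.29 = 0.71.
- Interim inflation factor 1.02; 572 patients in total.

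**The plan's own figure.** The two-proportion formula with pooled variance gives 199 per arm for 40% against 54%. Then 199 / 0.71 = 280.3 (stated 280), and 280 × 1.02 = 285.6 (stated 286). The sample size reproduces.

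**Assumptions the article does not supply**
- r = share of ischaemic patients reperfused. No rate is given, so a range is used.
- k = share of misdiagnosed patients reperfused. Taken as 0, then 10%.
- RIPerC has a 14-point effect in every ischaemic patient and none in haemorrhages or mimics.

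**Formula.** Ischaemic share of the 'no' side = 0.71(1 − r) / [0.71(1 − r) + 0.29(1 − k)]. Apparent effect = 14 × that share.

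**Split (iv), all misdiagnosed patients included, k = 0.** The 'yes' side shows 14 points throughout.

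| r | Patients on 'no' side | Ischaemic share | Apparent effect (points) |
|---|---|---|---|
| 20% | 491 | 0.66 | 9.3 |
| 30% | 450 | 0.63 | 8.8 |
| 40% | 410 | 0.60 | 8.3 |
| 50% | 369 | 0.55 | 7.7 |
| 60% | 328 | 0.50 | 6.9 |
| 70% | 288 | 0.42 | 5.9 |

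Example at r = 50%: 0.71 × 0.5 = 0.355; 0.355 / (0.355 + 0.29) = 0.55; 14 × 0.55 = 7.7.

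**Mimics lost, haemorrhages (15%) kept.** Share = 0.71(1 − r) / [0.71(1 − r) + 0.15] = 0.77, 0.70 and 0.65 at r = 30%, 50% and 60%. The apparent effect is 10.8, 9.8 and 9.2 points.

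**10% of misdiagnosed patients reperfused.** The 'yes' side is now diluted too. The ratio of the 'no' effect to the 'yes' effect is about 0.75, 0.62 and 0.56 at r = 30%, 50% and 60%.

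**Splits (ii) and (iii).** Their 'yes' groups are subsets of the 'yes' group in (iv), so the relevant r is smaller. With k = 0 the share is 0.66 at r = 20%, 0.69 at r = 10%, and tends to 0.71 as r falls.

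**After restriction to confirmed ischaemic stroke.** The share is 1 on both sides, so an equal 14-point benefit shows as 14 points in both.

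**Power on the 'no' side of (iv)** (equal arms, single look, 40% control rate in every diagnosis, which is a further assumption). At r = 30%, 50% and 70%, all randomised patients give 47%, 32% and 17%. Ischaemic patients only (284, 203 and 122 patients) give 66%, 52% and 34%. Under these assumptions the smaller, restricted stratum has more power.

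**The case against.** The strongest reply is that the article does not settle whether misdiagnosed patients enter the strata. The intention-to-treat set is undefined. The sample size divides by 0.71, as if those patients did not contribute to the comparison. Mimics have no assured 90-day mRS. The hypothesis is framed in ischaemic stroke. The per-protocol set might remove them, and subgroup populations are often left to a fuller document.

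Part of this stands. The size must be conditional, and a case with mimics lost belongs in it. But the article does name the intention-to-treat set, keeps haemorrhages to 90 days, and gives the splits for all objectives without a diagnostic limit. Followed as written, the confounding is there. A per-protocol repeat is only a sensitivity analysis, and nothing says that it drops misdiagnosed patients. If restriction is intended, one sentence would say so.

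A reader might infer more than the article supports:
- That the effect would look about half as large. Exactly half needs 1 − r = 0.29 / 0.71, so r = 59%, with k = 0 and mimics retained, and then only in (iv). The article gives no such rate.
- That haemorrhage patients would carry harm into the stratum. Nothing in the article points to such harm.
- That a benefit would certainly be reported as confined to reperfused patients. The article states no rule for comparing strata.
- That the overlapping splits lose the patients given rtPA alone. They can be recovered as the 'yes' group of (iv) minus the 'yes' group of (ii), so exclusive groups are mostly a matter of presentation.

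It is also fair that the same dilution reaches the main analysis: 14 × 0.71 = 9.9 points. Defining the analysis set there would help, but would not by itself fix the population for the strata.

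**Conclusion.** The point holds in conditional form. As written, splits (ii) to (iv) confound reperfusion status with diagnosis, and an equal benefit in ischaemic patients would look smaller where there was no reperfusion. On the 'no' side of (iv) the apparent effect is about 66% down to 42% of the true one for 20% to 70% reperfused. This assumes no effect and no reperfusion in misdiagnosed patients, all of whom are analysed. It is about 77% to 65% (30% to 60% reperfused) if mimics drop out. It is less marked in (ii) and (iii), and also if some misdiagnosed patients are reperfused. The direction is robust across these plausible cases; no single figure is. These are secondary analyses and the primary result is untouched by this point, but the change is worth making.

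**What to change.** In Stratified Analysis, state that splits (ii) to (iv) are run in patients with confirmed ischaemic stroke. Report haemorrhages and mimics as separate rows, and keep the all-randomised version as a sensitivity analysis. If the restriction was always intended, say so.

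The cost is about one sentence and no new data, since Table 2 already records AIS confirmation and reperfusion therapies. There are two drawbacks. Confirmation is completed after randomisation, so the restricted groups are not strictly protected by it; the all-randomised version is kept for that reason. The strata also become smaller: at 50% reperfused, the 'no' side of (iv) goes from 369 to 203 patients.

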# *Patients treated with intravenous rtPA and/or EVT will undergo neuroimaging at 24 h*.

### Randomization

First, patients will be stratified using the rapid arterial occlusion evaluation (RACE) scale score (14) and then, they will be randomly allocated in blocks of size four, to either receive remote ischemic conditioning (RIPerC group) or sham in the ambulance. An on-call physician not involved in the study will perform the randomization using a computer program located in a web server.

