### Intervention

RIPerC will consist of automatically delivered five cycles of electronic tourniquet inflation to the upper non-paretic limb, each lasting 5 min and separated by 5 min of cuff deflation. The cuff will be inflated to 200 mmHg and it will be applied to the opposite arm to the one experiencing motor and/or sensory deficit in order to reduce the risk of phlebitis and to maintain the somatosensory stimuli. RIPerC will be initiated by the ambulance staff during transportation and it will be finished for all patients in the ambulance or during Hospital admission. All patients in both groups will be treated according to conventional care procedures following international guidelines. Thus, mechanical thrombectomy and intravenous fibrinolysis will be allowed. Revascularization therapies will not be delayed due to the study. The non-interventionist group will use a sham device. It will simulate vibration of the device but no inflation will be performed. Discomfort and complications related to RIPerC will be recorded.

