## Discussion

RIPerC emerges as an interesting neuroprotective strategy (5). Our study improves the previous limited experience in humans (8, 11). It includes all AIS with symptom onset within 8 h and not only intravenous alteplase treated patients (11). According to the animal model, it is effective when applied both alone and in combination with revascularization therapies (22, 23). Although few studies have been published about the effect of RIC in AIS, some important issues have been learned (8–11). As in Hougaard's trial (11) and in most of the trials involving patients with myocardial infarction (7, 24) it is applied it in the ambulance, as soon as possible, in order to induce the maximum effect. This action seems to be safe although the definitive diagnosis will not be established until the arrival at the hospital. To date, no serious adverse effects have been reported in RIC studies (5, 7–11, 25). The recent RCT published by Pico et al. failed to demonstrate an effect of RIC in the final infarction size in AIS. One explanation of their neutral results was that the treatment with RIC was performed too late during or after the receipt of reperfusion therapies (10). In addition, we will increase the number of cycles to five. Most RIC trials use the four-cycle protocol (7, 11) due to tradition. The ischemic conditioning phenomena was first demonstrated using this protocol in an animal model of myocardial infarction (26). Recent studies in animal models address the need to increase the number of cycles in order to optimize the efficacy of RIPerC (27). Some other recent successes in remote ischemic preconditioning (28) and chronic postconditioning (29) in AIS patients have used the 5-cycle protocol. Increasing the duration of the cycle to 10 min does not offer any further protection (27). Although the quantity of muscle mass affects the efficacy of the intervention, we decided to perform the RIPerC on an upper arm rather than on a leg for safety reasons as up to one in four AIS patients have silent peripheral arterial disease defined by a low ankle-brachial index (30). One of the main shortcomings of the previously mentioned Hougaard's trial (11) was that fewer than one out of three patients complete the four cycles of limb ischemia. We will therefore use an automatic device. To avoid misdiagnosis only subjects with RACE score of >0 and RACE motor items >0 will be included. Finally, according to the stroke treatment academic industry roundtable (STAIR) recommendations a clinical endpoint would clearly evaluate the utility of applying RIPerC in AIS patients.

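### Outcome by number of cycles finished is not a randomised comparison and can show a dose-response gradient when RIPerC has no effect

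*Protocol article*

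**What the plan says.** Under Randomization, "patients will be stratified using the rapid arterial occlusion evaluation (RACE) scale score", and then "they will be randomly allocated in blocks of size four, to either receive remote ischemic conditioning (RIPerC group) or sham in the ambulance". The Intervention section has ambulance staff start treatment during transport. Table 2 lists randomisation and RIC/sham application under the prehospital column and reperfusion therapies under admission.

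The Intervention section describes sham as device vibration without inflation, says that reperfusion will not be held up by the study, and says of RIPerC that "it will be finished for all patients in the ambulance or during Hospital admission".

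The Stratified Analysis section then states: "All objectives will be assessed in the following stratified analyses". Five factors follow: sex; three based on reperfusion actually received, among them "depending on whether patients have undergone thrombectomy" and "whether patients have undergone thrombectomy or treated with rtPA"; and (v) the "number of cycles of inflation and deflation finished to evaluate a possible dose-response effect".

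The main analysis, under Statistical Analyses, is by intention to treat, with a per-protocol repeat as a sensitivity analysis.

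**The concern.** Of the five factors, only sex is fixed before allocation. Factor (v) is the most exposed, because the protocol names both the variable and the causal question it is meant to answer.

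Nobody is allocated to a number of cycles. Five 5-minute inflations with four 5-minute gaps take 5×5 + 4×5 = 45 minutes, beginning in an ambulance. A patient who stops short may do so because of discomfort, deterioration or urgent reperfusion. The article does not list the reasons, but these are plausible and each may carry prognostic information about the 90-day mRS.

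Sham offers no clear control. Read literally, every sham patient finishes zero inflation cycles, and the analysis becomes a non-randomised comparison within the RIPerC arm. If device cycles are counted instead, a vibrating cuff and one inflated to 200 mmHg may be tolerated differently, so patients with the same count in the two arms need not be alike.

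At stake is interpretation. A neutral trial could be presented as showing benefit in those who finished, and a positive one could be given a biological gradient that its design cannot support.

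**Working it through.** **The plan's own figures.** This point turns on no stated number, but the 14-point design effect is used below as a yardstick, so the calculation behind it was checked. For 40% against 54%, two-sided 0.05, 80% power and no continuity correction:

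n = [1.960·√(2×0.47×0.53) + 0.842·√(0.40×0.60 + 0.54×0.46)]² / 0.14² = 198.3, so 199 per arm.

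Allowing for 29% misdiagnosis, 199/0.71 = 280.3 (stated: 280). Then 280×1.02 = 285.6, so 286 per arm and 572 in total, as stated.

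**Timing of each stratum variable.**

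| Factor | When known | Baseline? |
|---|---|---|
| (i) sex | before randomisation | yes |
| (ii)–(iv) thrombectomy and/or rtPA | at admission, after RIPerC/sham has started | no |
| (v) cycles finished | during or after treatment | no |

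**Factor (v) with zero RIPerC effect.** The only document inputs are the 40% control rate and 286 per arm; the rest are assumptions. Half the patients are severe (25% good outcome) and half mild (55%), giving 0.5×25% + 0.5×55% = 40%. Mild patients finish all cycles 90% of the time; severe patients finish with probability c.

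- Finishers: (0.5×0.90×0.55 + 0.5×c×0.25) / (0.45 + 0.5c)
- Non-finishers: (0.5×0.10×0.55 + 0.5×(1−c)×0.25) / (0.05 + 0.5(1−c))
- Sham finishers: 40%, assuming 90% of sham patients finish whatever their severity

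At c = 0.50: finishers 0.31/0.70 = 44.3%; non-finishers 0.09/0.30 = 30.0%; gap 14.3 points.

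| Severe patients finishing | Finishers | Non-finishers | False gap (points) | Chance of p<0.05 among 286 RIPerC patients | RIPerC finishers minus sham finishers (points) |
|---|---|---|---|---|---|
| 90% | 40.0% | 40.0% | 0 | 5% | 0 |
| 80% | 40.9% | 35.0% | 5.9 | 11.5% | 0.9 |
| 70% | 41.9% | 32.5% | 9.4 | 26.8% | 1.9 |
| 60% | 43.0% | 31.0% | 12.0 | 46.3% | 3.0 |
| 50% | 44.3% | 30.0% | 14.3 | 65.4% | 4.3 |

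The significance column is a normal approximation: Φ(d/SE − 1.96) + Φ(−d/SE − 1.96), with unpooled SE. At c = 0.50 the group sizes are 286×0.70 = 200.2 and 286×0.30 = 85.8, so SE = √(0.443×0.557/200.2 + 0.30×0.70/85.8) = 0.061.

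**Thrombectomy strata with zero RIPerC effect on outcome.** Same patient mix; assumed sham thrombectomy rates are 50% in severe and 5% in mild patients. Good outcome in sham is then (0.5×0.50×0.25 + 0.5×0.05×0.55)/0.275 = 27.7% with thrombectomy and (0.5×0.50×0.25 + 0.5×0.95×0.55)/0.725 = 44.7% without.

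- If RIPerC does not change who is treated, the difference between arms is 0 in both strata.
- If the RIPerC rates become 40% severe and 10% mild, good outcome is (0.05 + 0.0275)/0.25 = 31.0% with thrombectomy and (0.075 + 0.2475)/0.75 = 43.0% without: false differences of +3.3 and −1.7 points. This was the largest shift examined.

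**The case against.** The best defence is that factor (v) is one secondary look at departures from the planned course, that the primary result rests on intention to treat, and that an automatic device should leave few patients short of five cycles. Near-complete finishing would leave little to analyse. The table also shows no bias when finishing is unrelated to severity, and the sham-finisher comparison moves by only about 4 points at most. All of this limits the damage. None of it supports the stated purpose, because the patients who do stop short are still not a randomised group.

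Several stronger readings are tempting, and the documents do not carry them:

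- **The reperfusion strata are as badly biased as the cycle strata.** Within-stratum bias needs allocation to alter who receives thrombectomy or rtPA. Both arms get guideline care, reperfusion is not delayed, and these strata address the stated hypothesis about patients treated with revascularisation or not. An effect on early improvement or blood pressure could open the path, but the assumed shifts give only about 3 points.
- **A very large spurious gradient should be expected.** Assuming, say, 60% good outcome in finishers and 30% in the rest yields 30 points, but that is a single chosen pair. The range above is 0 to about 14.
- **False positives are close to certain.** Crossing about 14 outcomes with about 14 strata gives 196 tests and 196×0.05 = 9.8 expected errors. That requires six populated cycle levels, each tested between arms at 5%. The article says only that objectives will be assessed, a dose-response question would usually be one trend, and factors (ii)–(iv) overlap.
- **The Intervention section contradicts factor (v).** Finishing for all patients is the planned course; an analysis by cycles finished deals with departures from it. The remark that "fewer than one out of three patients complete the four cycles of limb ischemia" describes an earlier trial and is the reason given for the automatic device.
- **The article omits interaction tests.** A condensed article may leave these to an analysis plan that is not shown.

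**Conclusion.** The concern holds for factor (v). As written, it assigns a dose-response question to a non-randomised variable measured after treatment starts, without a clearly comparable sham count. With no true effect, the false finisher gap runs from 0 to about 14 points. The upper end matches the trial's 14-point design effect and is reached only if 50% of severe patients finish against 90% of mild ones. The range rests on the assumed severity mix, outcome rates and finishing rates; the article gives no finishing data for this trial.

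For factors (ii)–(iv) the concern is conditional and probably small. Sex is unaffected. A reader should not infer that the primary intention-to-treat comparison or the sample size of 572 is compromised: neither uses these strata.

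**What to change.** 1. Report the number of cycles finished descriptively by arm, stating what counts as a cycle in the sham arm, and remove the statement that factor (v) evaluates dose-response.
2. If an exposure effect is wanted, replace factor (v) with an analysis using the randomised arm as instrument. State its assumptions: allocation affects outcome only through the cycles received, and the dose effect has a specified shape. One binary instrument cannot recover a curve over zero to five cycles without that shape. With a linear effect and zero dose in sham, the estimate is the intention-to-treat difference divided by the mean number of cycles finished in the RIPerC arm.
3. Label factors (ii)–(iv) exploratory. Base subgroup claims on baseline factors: sex, RACE stratum and onset-to-randomisation time (eligibility already requires a known onset). A treatment-by-subgroup interaction estimate with confidence interval is preferable to separate within-stratum results.

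The cost is a change of wording and, if option 2 is taken, one modest extra analysis. No change to conduct or recruitment is needed. The downside is a weaker dose-response claim.
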